### Participants and enrolment

Patients with recurrent glioblastoma who are referred for Gamma Knife treatment at Haukeland University Hospital, the national reference center for stereotactic radiosurgery in Norway, will be screened for eligibility. Those who meet all study criteria and provide informed consent will be enrolled and offered participation in the trial.

### Inclusion and exclusion criteria

The inclusion criteria for this study require that participants must be ≥18 years of age, have histologically confirmed glioblastoma (World Health Organization WHO grade 4) with a first or second recurrence as defined by Response Assessment in Neuro‑Oncology (RANO) criteria, and that they have previously undergone maximal safe resection followed by radiotherapy with concomitant temozolomide. Eligible patients must be suitable candidates for Gamma Knife stereotactic radiosurgery, with a recurrent lesion measuring 3 cm or less (≤ 15 cm³) on MRI obtained within the preceding 30 days prior to treatment. Functional status must be a Karnofsky Performance Status ≥70 and estimated life expectancy >12 weeks. To ensure adequate organ function, baseline laboratory values obtained within 7 days before first study dose must meet all of the following thresholds: absolute neutrophil count ≥1.0 × 10⁹/L without the support of filgrastim; platelet count ≥100 × 10⁹/L; hemoglobin ≥100 *g*/L; total bilirubin <1.5 × the upper limit of normal (ULN), except patients with Gilbert’s syndrome who may enroll if total bilirubin <51.3 µmol/L, alanine aminotransferase (ALT) and aspartate aminotransferase (AST) <3 × ULN; serum creatinine <1.5 × ULN, international normalized ratio (INR) <1.4. At least 4 weeks must have elapsed since any prior systemic anti‑cancer therapy, and all treatment‑related toxicities must have recovered to Grade 1 or lower before enrollment. All participants must provide written informed consent prior to any study‑specific procedures. .

Exclusion criteria apply to patients with known allergy or hypersensitivity to sulfasalazine, sulfonamides, salicylates, or related excipients, as well as those receiving or planning to receive temozolomide or other systemic anti‑tumor therapies during the study period. Individuals previously treated with sulfasalazine after their glioblastoma diagnosis, or those participating in a pharmacokinetic or immunotherapy trial within the past four weeks, will also be excluded. Additional exclusion criteria include medical conditions that could interfere with safe participation, such as glucose‑6‑phosphate dehydrogenase deficiency; significant cardiac (New York Heart Association functional classification III–IV), renal (chronic kidney disease (CKD) 3–5), or hepatic impairment; severe asthma or a history of severe allergic reactions; porphyria; erythema multiforme; intestinal or urinary obstruction; and the presence of another active malignancy or multiple sclerosis. Patients who are pregnant or breastfeeding, as well as those with psychiatric or cognitive disorders that impair the ability to provide informed consent or adhere to study procedures, will similarly be excluded.

#### Washout requirements for prior therapies at recurrence

Participants may have received one prior treatment for an earlier recurrence and may enroll at first or second recurrence, however, they must be bevacizumab‑naïve, as prior bevacizumab exposure may alter vascular permeability and confound safety assessments. A minimum of four weeks must have elapsed since any prior local or systemic anti‑cancer therapy, including alkylating agents such as temozolomide rechallenge, lomustine, or PCV, and all treatment‑related toxicities must have recovered to Grade ≤ 1 before study treatment.

Participants may have undergone resection or GKRS for a prior recurrence, but GKRS to the same previously treated lesion and prior fractionated reirradiation for recurrence are not permitted.

Prior exposure to investigational agents, including participation in pharmacokinetic or immunotherapy trials, or use of device‑based therapies such as tumor treating fields, is permitted only if ≥4 weeks have elapsed before enrollment and all toxicities have resolved to Grade ≤ 1. Tumor treating fields are not in routine use in Norway, but prior use does not preclude participation. No additional washout restrictions apply.

### Sample size

As is standard for phase I dose‑escalation studies using a 3 + 3 design, no formal sample size calculation was performed. The total number of participants is determined by the number of dose‑escalation cohorts required to identify the maximum tolerated dose. Based on the planned four dose levels, the study is expected to enroll between 12 and 24 patients, which is consistent with conventional 3 + 3 methodology and provides an adequate basis for assessing safety and tolerability in this early‑phase setting.

### Intervention

Participants are admitted to the hospital for five days, from Monday to Friday. Screening procedures and baseline assessments are conducted on the day of admission (Day 0). The intervention takes place over the subsequent three days (Day 1–3), and participants are discharged on Day 4 following an end‑of‑treatment safety evaluation.

During the intervention period, participants receive oral sulfasalazine in the form of enteric‑coated 500 mg tablets administered once daily for three consecutive days. Dose escalation follows a traditional 3 + 3 design, in which cohorts of three to six participants receive one of four predefined dose levels: 1.5 *g*, 3 *g*, 4.5 *g*, or 6 *g* once daily. All doses are administered under the supervision of a study nurse, who monitors intake and assesses acute tolerability.

On the third intervention day, approximately 6 hours after participants receive their third and final sulfasalazine dose, they undergo stereotactic gamma knife radiosurgery. GKRS is delivered with a standard prescription dose of 12 Gy to the contrast‑enhancing tumor volume.

### Justification of dose regimen

The selection of a once‑daily, 3‑day sulfasalazine regimen at dose levels from 1.5 to 6.0 *g* is based on pharmacokinetic considerations and on prior clinical experience, including the study by Robe et al [16], who used the same dose range in patients with malignant gliomas after primary treatment. Sulfasalazine is metabolized by intestinal bacteria to sulfapyridine and 5‑ASA. However, it is the parent compound and not its metabolites that inhibits xCT and provides the radiosensitizing effect. Most sulfasalazine undergoes colonic cleavage, with <15% reaching systemic circulation, and the serum half‑life is approximately 12.7 hours[18], although with substantial interindividual variability. With this pharmacokinetic profile, administering sulfasalazine over 3 days is expected to gradually increase intracellular drug exposure and reduce glutathione levels in tumor cells before GKRS.

The sulfasalazine dose required to achieve high occupancy of the xCT antiporter, as well as the turnover rate of sulfasalazine bound to xCT in patients, is not yet known. As the optimal biologically effective dose remains undefined, the present trial includes several dose levels in a standard dose‑escalation design to identify the highest dose considered safe. Robe et al. administered 1.5, 3.0, 4.5, and 6.0 *g* daily for a substantially longer duration (mean 32 days) as monotherapy to patients with recurrent malignant glioma (mean tumor volume 68 mL) until progression or treatment‑limiting toxicity. Although all patients experienced adverse effects including two fatalities there was no correlation between dose level and toxicity, and notably, six of seven grade 4 events and both deaths occurred in the lowest‑dose cohort (1.5 *g*). Importantly, in all cases where sulfasalazine was discontinued due to side effects, toxicity emerged far later than the brief 3‑day exposure used in our trial. Our study includes patients with considerably smaller tumor volumes (<15 mL) and uses stepwise dose escalation to ensure safety. In this context, employing the same dose range as in Robe et al. is considered feasible with acceptable risk. Moreover, these dose levels align with those used safely for decades in chronic inflammatory diseases such as rheumatoid arthritis and Crohn’s disease.

Although pharmacological data directly demonstrating sulfasalazine penetration of the intact blood–brain barrier are lacking, both the findings from Robe et al. and preclinical experiments detecting sulfasalazine in brain tumor tissue after 3 days of dosing, together with clear radiosensitizing anti‑tumor effects in glioblastoma xenograft models treated with GKRS, indicate that sulfasalazine reaches tumor tissue through the disrupted blood–brain barrier.

Once‑daily dosing is selected for feasibility and consistency with preclinical experiments and facilitates safe administration under direct nurse observation during inpatient hospitalization ensuring adherence. Although pill burden increases across dose levels (3 - 12 x 500 mg tablets), once‑daily administration is operationally simpler than divided dosing while maintaining alignment with the expected radiosensitization window. A single daily dose produces a well‑defined serum concentration peak 3 - 12 hours after ingestion, allowing predictable pharmacodynamic timing relative to GKRS.

#### Concomitant medications and supportive care

Chronic medication with sulfasalazine and ongoing treatment with temozolomide at study inclusion are exclusion criteria. All other prescribed medications may continue unchanged, including stable antiepileptic therapy. Dexamethasone is continued at the dose prescribed at admission with no required protocol‑mandated stabilization period. When clinically indicated due to asymptomatic or symptomatic peritumoral edema on baseline MRI, a pre‑procedural dose of dexamethasone (4 mg) may be administered before GKRS together with antacid prophylaxis such as ranitidine according to institutional practice.

All patients are offered premedication consisting of oxazepam 10 mg or diazepam 5 mg according to institutional practice prior to GKRS. Stereotactic frame placement is performed under local anesthesia with subcutaneous lidocaine with adrenaline (10 mg/ml up to 20 ml), with additional infiltration (up to 10 ml) as needed, which is the primary method of pain control. Additional anxiolysis or light sedation during GKRS is permitted when clinically appropriate.

Supportive care follows routine neurosurgical practice. Paracetamol, tramadol, or morphine is used as needed for headache or procedural discomfort when local anesthetic refill is insufficient, metoclopramide or ondansetron is administered for nausea and zopiclone is used for insomnia on the evening before or the day of GKRS. Over‑the‑counter medications, vitamins, herbal supplements, and other chronic treatments are allowed at the investigator’s discretion provided they do not interfere with study treatment or confound safety assessments. All concomitant medications are documented in the case report form, including a separate record of steroid use and any dose changes over time

#### Management of adverse events related to sulfasalazine and stopping rules

Sulfasalazine is administered once daily for only 3 days and has a plasma half‑life of 12.7 h therefore, drug‑related toxicity is expected to occur during or shortly after this brief exposure. Given the 24‑hour interval between a total of only three doses and scheduled daily laboratory monitoring, treatment holding is not feasible, only discontinuation criteria are applicable.

Gastrointestinal intolerance (nausea, vomiting, abdominal pain, diarrhea), hypersensitivity reactions (rash, fever, urticaria), hepatotoxicity (elevated bilirubin or transaminases) and hematologic toxicity (neutropenia, thrombocytopenia, anemia) of Grade ≤ 2 will be managed with symptomatic therapy (e.g., antiemetics or antihistamines) and close clinical and laboratory monitoring, with continued sulfasalazine treatment. Grade 3 neutropenia or thrombocytopenia will warrant discontinuation of sulfasalazine. Dosing may proceed only if the abnormality returns to Grade ≤1 within 24 h without intervention. Hematologic toxicities persisting for >24 h, any hematologic toxicity of Grade >3, and all Grade ≥3 gastrointestinal intolerance, hypersensitivity reactions, or hepatotoxicity will lead to permanent discontinuation of sulfasalazine and notification of the DMC

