To ensure adequate safety maturation, a minimum of 1 week must elapse after the completion of treatment on Day 3 in the preceding participant before the next participant is enrolled. Missed doses, dose reductions and early discontinuation will not remove a participant from DLT evaluability. Hospitalization does not remove a participant from DLT evaluability unless it is due to a pre‑planned elective procedure or expected disease progression rather than an adverse event related to sulfasalazine or GKRS. Serious adverse events (SAEs) will be reported according to regulatory timelines. Late radiation‑related toxicity will be monitored at 3, 6, 9 and 12 months post-GKRS, but will not influence dose‑escalation decisions.

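### The hematologic stopping text conflicts with itself on holding, on persistent low-grade toxicity and on grade 3 anemia, so one laboratory course can lead to different actions

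*Protocol article*

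**What the plan says.** All the rules at issue stand in one section of the protocol article, *Management of adverse events related to sulfasalazine and stopping rules*.

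- General statement: "treatment holding is not feasible, only discontinuation criteria are applicable". The reasons given are the 24-hour spacing of only three doses and the daily laboratory tests.
- Grade 2 or lower: neutropenia, thrombocytopenia and anemia are listed with the other toxicities and are handled by symptomatic treatment and monitoring, "with continued sulfasalazine treatment". No time limit is given.
- Grade 3, two cell lines only: "Grade 3 neutropenia or thrombocytopenia will warrant discontinuation of sulfasalazine". The next sentence reads "Dosing may proceed only if the abnormality returns to Grade ≤1 within 24 h without intervention".
- Last sentence: "Hematologic toxicities persisting for" more than 24 h, with no grade attached, lead to a permanent stop and a notice to the DMC. So does any hematologic toxicity above grade 3.

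Two rules elsewhere bear on the consequence, both under *Primary outcome*. A grade 3 or higher event in the window that is at least possibly related to the trial intervention is a DLT. On stopped or incomplete dosing, the text says "Missed doses, dose reductions and early discontinuation will not remove a participant from DLT evaluability".

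**The concern.** A stopping rule should turn one observed result into one action. Here three kinds of hematologic result do not get one clear action.

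1. The text rules out holding, then sets up a wait-and-resume step for grade 3 neutropenia or thrombocytopenia.
2. Low-grade toxicity that lasts falls under a rule to continue and, on the literal wording, under a rule to stop for good.
3. Grade 3 anemia falls between the grade 3 sentence, which names only two cell lines, and the sentence that starts above grade 3.

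This is a patient-protection rule in a first-in-human combination, with cohorts of three to six. The rule also fixes how much drug a participant has received when counted at a dose level, and whether the DMC hears of the case through this route. The third dose is the one most exposed to the conflict over persistence, and it is the dose given about six hours before radiosurgery.

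**Working it through.** There is no planned figure to reproduce, since the section gives rules and not numbers. The check is to read each sentence as a rule (toxicity, grade, duration, action) and count the actions that each result receives while doses remain.

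| Hematologic result | Action on the literal text | Number of actions |
|---|---|---|
| Grade 1–2, up to 24 h | Continue | One |
| Grade 1–2, over 24 h | Continue; also permanent stop with DMC notice | Two |
| Grade 3 neutropenia or thrombocytopenia, back to grade 1 or lower within 24 h unaided | Discontinue; also dosing may go on | Two |
| Grade 3 neutropenia or thrombocytopenia, over 24 h | Permanent stop with DMC notice | One |
| Grade 3 anemia, up to 24 h | None stated | None |
| Grade 3 anemia, over 24 h | Permanent stop with DMC notice, only through the clause without a grade | One, if that clause covers it |
| Above grade 3 | Permanent stop with DMC notice | One |

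**Why the grade 3 step works as a hold.** Doses are 24 h apart. Let the event begin t hours before the next scheduled dose, with 0 < t < 24. At that dose time the recovery window still has 24 − t hours to run. If t is 8 (an illustrative value), 16 h remain. A participant who has not yet recovered cannot be dosed, but has not met the condition for a permanent stop either. That state is a hold. The last sentence also keeps the word permanent for its own list of cases, which implies that the earlier discontinuation can be temporary.

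**What the persistence conflict can do to exposure.** Assume that the toxicity begins after dose 1, since the section concerns events related to sulfasalazine.

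- At dose 2, at most 24 h have passed since dose 1, so toxicity cannot yet have lasted more than 24 h. Dose 2 is not affected.
- At dose 3, up to 48 h have passed, so the clause can apply. Only dose 3 is at stake.
- If the clause applies: 2/3 = 67% of the planned total. If the continue rule applies: 3/3 = 100%.

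| Level (g per day) | Three doses (g) | Two doses (g) |
|---|---|---|
| 1.5 | 4.5 | 3 |
| 3 | 9 | 6 |
| 4.5 | 13.5 | 9 |
| 6 | 18 | 12 |

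At 4.5 g, two doses give 9 g, equal to the planned total at 3 g. At 6 g, two doses give 12 g, less than the 13.5 g planned at 4.5 g. These are cumulative amounts; the single dose taken is still that of the assigned level.

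**Effect on the DLT count.** A related grade 3 event is a DLT whether dosing stops or goes on. Persistent grade 1–2 toxicity is not a DLT under either reading, and the participant stays evaluable under either reading. So the classification of an observed event and the denominator do not move; the exposure behind them can.

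**The case against.** The strongest defense is that the section can be read in sequence. The persistence clause comes straight after the grade 3 sentences and mirrors their 24-hour test: recovery in time allows dosing, persistence ends it. On that reading it applies to grade 3 only, and grade 2 or lower simply continues. Likewise, if recovery is seen before the next scheduled dose, no dose is held.

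Part of this stands. The second conflict is an ambiguity from a missing grade and is less certain than the first. But the neighboring clauses of the same sentence do state grades, so the omission is not plainly shorthand. On the first conflict, the sequence reading covers only a participant who recovers before the dose falls due; it does not cover one who is still inside the window at that time.

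Several stronger readings are tempting, and the documents do not support them.

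- A reader might infer that different sites would act differently. The trial is single-center, at one hospital.
- A reader might infer that the evaluability rule on missed and reduced doses contradicts the stopping section. The stopping section never says that such doses cannot occur, and the evaluability rule only says how participants are counted.
- A reader might infer that a participant could be stopped after one dose (33%) because of the persistence conflict. The 24-hour spacing rules that out.
- A reader might infer that grade 3 anemia has no rule at all. Beyond 24 h the clause without a grade reaches it, if that clause is taken literally.
- A reader might infer that the hemoglobin and neutrophil limits for entry make persistent low-grade toxicity likely. Those are values before treatment, while the section concerns events related to the drug.

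It is also fair that daily laboratory tests on Days 0–4 and DMC review of grade 3 or higher events limit the safety effect, and that keeping early stoppers evaluable is an explicit choice of the protocol.

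**Conclusion.** The concern holds as an internal conflict in a stated stopping rule. The clash between ruling out holds and allowing dosing to go on after grade 3 neutropenia or thrombocytopenia is clear on the text. The clash over persistent grade 1–2 toxicity holds on the literal text and depends on the clause having no grade. The gap for grade 3 anemia is certain for 24 h or less; beyond that it depends on the same clause.

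The consequence is that two investigators at the one center, or one investigator with two patients, could act differently on the same result. Under the persistence conflict the difference is one dose of three, 67% against 100% of the planned total, together with whether the DMC is notified. In both cases the participant counts as evaluable without a DLT, provided that no other DLT occurs. This rests on onset after dose 1 and on 24-hour dosing. The documents give no figure for how often such courses would arise, so no effect on the chance of escalation can be derived. The classification of a related grade 3 event as a DLT is not affected.

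**What to change.** Reconcile the sentences of the stopping section with one another. The revised text should:

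- say whether dosing can be suspended and resumed, and make the general statement agree with the grade 3 sentences;
- state the grade or grades to which the persistence clause applies;
- give an action for grade 3 anemia, including anemia that resolves within 24 h;
- give each hematologic grade and duration exactly one action and one DMC-notification rule.

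Which action is right in each case is for the sponsor and the DMC to decide. A short table of grade by duration would do it. The cost is one rewritten paragraph or table, with no added visits, tests or participants.

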### Screening and baseline assessments

Screening is performed on Day 0 following pre‑screening at referral to confirm eligibility. All screening procedures, baseline imaging, laboratory tests, and functional assessments are completed prior to the first sulfasalazine dose.

Baseline imaging includes MRI and [¹¹C]methionine PET to verify recurrent glioblastoma, evaluated according to RANO criteria and assessment of metabolic tumor activity using the maximum standardized uptake value (SUV_max_). GSH-edited MRS is obtained to quantify baseline glutathione levels in both tumor tissue and normal brain.

Clinical assessments include detailed medical history, complete physical examination, and vital signs. Laboratory evaluations encompass hematologic, renal, hepatic, electrolyte, and inflammatory profiles, and pregnancy testing is performed when indicated. Functional status is assessed using KPS, and participants complete the Functional Assessment of Cancer Therapy-Brain (FACT‑Br) questionnaire to document baseline patient‑reported outcomes related to neurological function and QoL.

### Follow‑up assessments

#### Primary outcome

The dose‑limiting toxicity (DLT) window is defined as Day 1 (first dose of sulfasalazine) through 30 days after the final sulfasalazine dose and gamma knife treatment on Day 3 during which adverse events will be recorded continuously. Adverse events will be graded from 1 to 5 according to Common Terminology Criteria for Adverse Events (CTCAE) version 4.0 [19,20]. For each AE, investigators will assign attribution using standard categories (unrelated, unlikely, possibly, probably, or definitely) to determine the causal relationship to sulfasalazine and GKRS. DLT is defined as any CTCAE v4.0 grade ≥ 3 adverse event occurring within this window, assessed by the investigator as at least possibly related to trial intervention. Adverse events considered to be clearly attributable to expected disease progression or pre-planned hospitalization admission (ie, elective or scheduled surgery arranged prior to the start of treatment) will not be reported as DLT. Similarly, treatment‑related effects expected following GKRS (e.g. pseudoprogression or increased peritumoral edema) and events listed in the sulfasalazine SmPC are not considered “unexpected” and are only classified as Suspected Unexpected Serious Adverse Reactions (SUSAR) if more severe in intensity or more frequent than anticipated.

Safety monitoring includes daily clinical evaluations of vital signs and laboratory testing (hematology, renal/hepatic function, electrolytes, C‑reactive protein, and urine analysis) during the 5-day hospitalization (Day 0–4) in conjunction with the 3-day intervention period (Day 1–3) and at outpatient follow‑up visits at 1, 2, and 4 weeks. MRI will be performed on Day 4 and at 4 weeks to detect early edema and other acute treatment‑related changes. The 4‑week visit will also include [¹¹C]methionine PET. Participant‑reported outcomes during the safety monitoring period will be collected using the FACT‑Br questionnaire at Day 0, Day 4, and weeks 1, 2, and 4. KPS will be assessed at the same timepoints.

Dose escalation follows the 3 + 3 design and proceeds only if no participant experiences a treatment‑related CTCAE v4.0 ≥ 3 adverse event. If one participant experiences a grade ≥ 3 event, the cohort will be expanded to six participants. The maximum tolerated dose (MTD) is defined as the dose preceding that at which 2 of 3 or 2 of 6 patients experience a grade 3 or higher adverse event within the DLT-window.

To ensure adequate safety maturation, a minimum of 1 week must elapse after the completion of treatment on Day 3 in the preceding participant before the next participant is enrolled. Missed doses, dose reductions and early discontinuation will not remove a participant from DLT evaluability. Hospitalization does not remove a participant from DLT evaluability unless it is due to a pre‑planned elective procedure or expected disease progression rather than an adverse event related to sulfasalazine or GKRS. Serious adverse events (SAEs) will be reported according to regulatory timelines. Late radiation‑related toxicity will be monitored at 3, 6, 9 and 12 months post-GKRS, but will not influence dose‑escalation decisions.

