### Study design

This is a phase I, single‑center dose‑escalation trial using a classic 3 + 3 design [17] to evaluate escalating doses of oral sulfasalazine administered for three days prior to GKRS with an anticipated recruitment period of 24 months. The dose will be escalated or de-escalated with diminishing fractions of the preceding dose (modified Fibonacci sequence), depending on the occurrence of adverse events grade ≥ 3.

Cohorts of three patients receive escalating once‑daily sulfasalazine doses (1.5, 3, 4.5, 6 g) for three days, with GKRS on Day 3. Escalation proceeds if no ≥ grade 3 toxicity occurs; a single ≥ grade 3 event expands the cohort to six; ≥2 events at a dose level in 3–6 participants define that dose as exceeding the maximum tolerated dose (MTD), with the preceding dose as the recommended phase 2 dose.

Each participant undergoes a three‑day treatment phase followed by clinical and radiological follow‑up for up to one year. This design allows systematic dose escalation while ensuring patient safety and assessment of early efficacy signals.

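### The DLT evaluability rule counts under-exposed participants without a DLT as full-dose non-events, which tilts the 3+3 toward escalation

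*Protocol article*

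**What the plan says.** The evaluability rule stands in the Protocol article under Follow-up assessments, Primary outcome: "Missed doses, dose reductions and early discontinuation will not remove a participant from DLT evaluability". The only exception there concerns hospitalization, which keeps a participant evaluable "unless it is due to a pre‑planned elective procedure or expected disease progression rather than an adverse event related to sulfasalazine or GKRS". Nothing in the article makes evaluability depend on how much sulfasalazine was taken or whether GKRS was given, and no replacement is provided for.

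The counts drive the primary endpoint. Study design states: "Escalation proceeds if no ≥ grade 3 toxicity occurs; a single ≥ grade 3 event expands the cohort to six". Primary outcome gives the rule for the MTD in these words: "defined as the dose preceding that at which 2 of 3 or 2 of 6 patients experience a grade 3 or higher adverse event". The full course, under Intervention, is sulfasalazine "administered once daily for three consecutive days", with GKRS on the third day. On enrolment, Sample size says: "Based on the planned four dose levels, the study is expected to enroll between 12 and 24 patients".

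The section on management of adverse events and stopping rules says that "treatment holding is not feasible, only discontinuation criteria are applicable". It then provides, after Grade 3 neutropenia or thrombocytopenia: "Dosing may proceed only if the abnormality returns to Grade" 1 or lower within 24 hours. In the same section, toxicity of Grade 2 or lower in the listed categories is managed symptomatically while dosing continues.

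**The concern.** A 3+3 design attributes each participant's outcome to the assigned dose level. A participant who stopped because of a DLT belongs in the count, since the assigned level produced the event. A participant who took only part of the course and had no DLT shows less about the full level, yet the rule gives that non-event full weight among the 3 or 6 that decide escalation.

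The error runs one way. If DLT risk does not decrease with exposure, under-exposed non-events lower the apparent DLT rate, make escalation likelier, and can place the MTD and the recommended phase II dose too high. With only three doses in the course, one missed dose is a third of the planned sulfasalazine.

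The article leaves several routes to under-exposure without a DLT: refusal, vomited or incomplete intake (3 to 12 tablets at a time, depending on level), withdrawal, and a stop for a Grade 3 or worse event judged unrelated, which is not a DLT by the protocol's definition.

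**Working it through.** **The plan's own figure.** Four levels of three give 4 × 3 = 12, and four levels of six give 4 × 6 = 24. The stated 12 to 24 reproduces. It contains no allowance for replacements.

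**Inputs from the article.** With 0 of 3 DLTs the dose is escalated. With 1 of 3 the cohort expands to six. Two or more DLTs mean that the level exceeds the MTD. I take 1 of 6 to permit escalation, as in a conventional 3+3; the article implies this without stating it outright.

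**Assumptions, not in the article.** The true DLT rate at full exposure is p. An under-exposed participant has DLT risk r × p, with r between 0 (no risk) and 1/2 (half the full risk). One of the first three is under-exposed, and the three added on expansion are fully exposed.

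**Formula.** P(escalate) = A0 + A1 × (1 − p)³, where A0 and A1 are the probabilities of 0 and 1 DLT in the first three.

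- All fully exposed: A0 = (1 − p)³ and A1 = 3p(1 − p)².
- One under-exposed: A0 = (1 − p)²(1 − rp) and A1 = 2p(1 − p)(1 − rp) + (1 − p)² × rp.

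**At p = 0.40.**

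- All fully exposed: 0.216 + 0.432 × 0.216 = 0.309.
- One under-exposed, r = 1/2: 0.288 + 0.456 × 0.216 = 0.386.
- One under-exposed, r = 0: 0.360 + 0.480 × 0.216 = 0.464.

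**At p = 0.50.**

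- All fully exposed: 0.125 + 0.375 × 0.125 = 0.172.
- One under-exposed, r = 1/2: 0.1875 + 0.4375 × 0.125 = 0.242.
- One under-exposed, r = 0: 0.250 + 0.500 × 0.125 = 0.312.

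**Across assumed rates.**

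| True DLT rate | All fully exposed | One of first three under-exposed (r = 1/2 to 0) |
|---|---|---|
| 0.33 | 43.4% | 50.8% to 58.2% |
| 0.40 | 30.9% | 38.6% to 46.4% |
| 0.50 | 17.2% | 24.2% to 31.2% |
| 0.60 | 8.2% | 13.7% to 19.1% |

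The direction does not depend on the reading of 1 of 6. The chance of 0 of 3 alone rises from 21.6% to 28.8-36.0% at p = 0.40, and from 12.5% to 18.8-25.0% at p = 0.50.

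**Information lost.** With 0 DLTs in n fully exposed participants, the one-sided 95% upper bound on the DLT rate is 1 − 0.05^(1/n). That is 63.2% for n = 3 and 77.6% for n = 2.

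**Dose modification, read side by side.** The evaluability rule under Primary outcome names dose reductions, while the stopping-rules section says that only discontinuation criteria apply. Within the stopping-rules section, holding is called not feasible, yet dosing may go on once a Grade 3 count recovers within 24 hours.

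**The case against.** The strongest reply is that this will seldom happen. The course is three doses, given in hospital with a study nurse monitoring intake, and the listed discontinuation triggers are Grade 3 or worse, which are DLTs if at least possibly related. That stands, and it limits the expected size.

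A reader might infer that participants will often stop for tolerability below Grade 3. The article does not support this, since the stopping-rules section continues dosing at Grade 2 or lower.

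A reader might also infer a much larger distortion by assuming that one in six or one in three of all participants is under-exposed and that their DLT risk falls from 40% to 5%. With p' = (1 − f) × 0.40 + f × 0.05, P(escalate) becomes 41% or 53%. The arithmetic is right, but the article supports neither assumption. Such frequencies sit badly with supervised dosing. Two doses at 6 g total 12 g, against 13.5 g for the full 4.5 g course, so one missed dose resembles a step down in total drug more than near-absence of exposure. DLTs can also come from GKRS, whose prescription is fixed at 12 Gy. Halving the risk to 20% instead gives 37% and 43%.

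The article reports that toxicity did not track dose level in an earlier glioma trial. This does not rescue the rule, because a 3+3 itself attributes outcomes to the assigned level.

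Counting everyone treated does guard against selective exclusion, and replacement details are often left to the full protocol. The first point is met by reporting both counts. The second does not apply, because the article states an unconditional rule. It is also fair that a stricter definition, which keeps partly exposed participants only when they have a DLT, leans the other way. A demand for all three doses would lean furthest, so the threshold should be the sponsor's to justify.

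**Conclusion.** The point holds with a limited size. As written, the rule lets an under-exposed participant without a DLT count as evidence that the full dose is tolerable, in the count that fixes the primary endpoint. The direction of the bias is secure if DLT risk does not decrease with exposure. Its size is illustrative only: the rises of roughly 7 to 16 percentage points at true rates of 40% and 50% are conditional on one of the first three being under-exposed, and the article gives neither DLT rates nor an expected frequency of incomplete dosing. Overall, such cases should be few.

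On dose modification, a reader might infer that the two sections disagree about whether missed or held doses can occur at all. They do not go that far: the evaluability rule never mentions holding, and the stopping-rules section never says that a dose cannot be missed. Two narrower conflicts remain, namely dose reductions against discontinuation only, and holding not feasible against dosing that may proceed after recovery.

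The change is worth making, because one participant is a third of an initial cohort and the correction is mainly wording.

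**What to change.** For escalation decisions, define a DLT-evaluable participant as one who either (a) had a DLT at any time after the first dose, or (b) received a minimum of the assigned sulfasalazine course, set and justified in advance by the sponsor, plus GKRS, and completed the DLT window. Replace participants who meet neither condition at the same dose level. Keep all treated participants in the safety tables, and report the DLT count among all treated beside the evaluable count, so that the effect of any replacement is visible.

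State in Sample size that replacements may take enrolment above 24. Reconcile the mention of dose reductions in the evaluability rule with the statement that only discontinuation criteria apply. Also reconcile, within the stopping-rules section, the statement on holding with the provision for continued dosing after recovery. Which clinical rule applies is for the sponsor to settle.

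The cost is a wording amendment and, given supervised inpatient dosing, at most an occasional extra participant.
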